### Study procedures

Preoperatively as well as six weeks, six months and one year postoperatively, patients will visit the outpatient clinic. Routine physical examination will be performed by the orthopedic surgeon.

Primary outcome measure–achievement of an overcorrection of 4° valgus alignment / hip-knee-ankle angle (HKA, in degrees)–will be measured after one year on a whole-leg radiograph (WLR) standing on one leg. The continuous differences in achievement of a valgus overcorrection and the deviation from 4° valgus are determined. A dichotomous outcome is achievement of a 2-6° valgus alignment.

Secondary outcome measures, posterior tibial slope (Moore-Harvey and Dejour-Bonin), patellar height (Insall-Salvati and Caton Index) and difference in leg length (cm) one year after surgery will be obtained. Pain severity (VAS; range 0–10), knee function and quality of life (KOOS), and walking distance (km) six weeks, three months, six months and one year after surgery will also be obtained.

### Sample size calculation

The sample size was calculated based on an expected increase of the success rate from 60% in the closed wedge HTO to 85% in the combined wedge HTO. A successful operative result is defined as achievement of a 2-6° valgus alignment. To detect such a difference with α= 0.05 and a power of 80%, we need to include 50 patients in each study group. To adjust for possible loss to follow-up, a total of 110 patients will be included in the study.

### Statistics

All data will be analyzed according to an intention-to-treat principle, implying that all patients who are randomized will be included in the analyses, and that they will be analyzed according to the group to which they were allocated. For those patients who will be lost to follow-up or will be re-operated during follow-up, the last available measurement or the last measurement will be forwarded (Last Value Carried Forward technique).

A multivariable linear regression method will be used to analyze the impact of LCW versus CWO HTO on postoperative alignment, posterior tibial slope, patellar height, leg length, VAS, KOOS, walking distance and patients with adverse events at the one-year follow-up. A multivariable logistic regression method will be used for the dichotomous outcome measures. Gender, age and baseline values for HKA angle, VAS knee, KOOS, walking distance, medial osteoarthritis more than joint space loss alone, and concurrent OA of the lateral compartment will be considered as possible confounders and are included in the regression models only if they change the relationship between dependent variable and type of HTO by at least 10%. The SPSS program will be used for the statistical analyses and a p-value of 0.05 is considered statistically significant.

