### Interventions

After randomization patients will undergo either a CWO HTO or a LCW HTO; all patients will be operated on by one of two orthopedic surgeons, both experienced in applying the two techniques so there will be no bias. Preoperative the wedge-correction is calculated aiming on 4° overcorrection.

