### Other study parameters

Potential confounding parameters, such as opposite cortex fractures, demographic data, length, weight and BMI will be recorded. Adverse events like re-operations, including hardware removal, will also be recorded**.**

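### Carrying the last value forward also governs adverse events, so unobserved time reads as event-free and a re-operation can freeze the status it should change

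*Protocol article*

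**What the plan says.** The Statistics section of the Protocol article begins with a general rule: "All data will be analyzed according to an intention-to-treat principle, implying that all patients who are randomized will be included", and "they will be analyzed according to the group to which they were allocated". Its next sentence deals with incomplete follow-up: "lost to follow-up or will be re-operated during follow-up, the last available measurement or the last measurement will be forwarded".

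The following paragraph names the outcomes for the regression models. The list ends with "leg length, VAS, KOOS, walking distance and patients with adverse events at the one-year follow-up". Adverse events therefore stand in the same list as alignment, pain and function, and no other population or missing-data rule is given for them.

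Two other sections bear on this. Under Other study parameters: "Adverse events like re-operations, including hardware removal, will also be recorded". Under Sample size calculation: "To adjust for possible loss to follow-up, a total of 110 patients will be included in the study". So the plan expects some loss, and one of the two triggers for carry-forward, re-operation, is itself on the list of adverse events.

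**The concern.** For a pain score or an angle, carrying the last value forward at least repeats something that was measured. For an event it does something different. A status of no event so far, carried to one year, asserts that nothing happened during time when nobody was looking. Re-operation and hardware removal can come late in the year, so this time is not empty of risk.

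The re-operation trigger adds a second problem. If a patient's first adverse event is the re-operation, the rule as written can forward the status from before it. Events after the re-operation could also go uncounted.

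Both readings can only lower the recorded complication rates. The comparison between techniques may then shrink on the difference scale or, if loss is uneven, shift either way.

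**Working it through.** **The two statements about re-operation side by side.** Other study parameters makes re-operation an adverse event. Statistics makes re-operation a reason to forward an earlier value. Adverse events are an outcome under Statistics with no exception. Taken together and literally, the event that should change a patient's status is also what fixes the status at its earlier value. The article does not give the share of events that are re-operations, so this part is not sized here.

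**The plan's own figures.** For 60% v 85% success, two-sided α of 0.05 and 80% power, the usual two-proportion formula without continuity correction gives

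- n = [1.96 × √(2 × 0.725 × 0.275) + 0.842 × √(0.60 × 0.40 + 0.85 × 0.15)]² / 0.25² = 48.9, so 49 per group, against 50 stated.

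The sample size reproduces and is not in question. The allowance for loss is 110 − 2 × 50 = 10 patients, or 10/110 = 9.1%. Spread evenly, that is 5 of 55 per arm.

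**Assumptions.** The article gives no adverse event rates. I assume a one-year risk of at least one event of 20% with the lateral closing wedge (LCW) and 10% with the combined wedge (CWO). Let L be the share lost and m the share of their events that is missed because they are carried forward as event-free. Then

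- recorded risk = true risk × (1 − L × m).

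**Even loss, L = 5/55 in each arm.**

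| Share of lost patients' events missed | LCW | CWO | Difference | Risk ratio |
|---|---|---|---|---|
| None (m = 0) | 20.0% | 10.0% | 10.0 points | 2.0 |
| Half (m = 0.5) | 19.1% | 9.5% | 9.5 points | 2.0 |
| All (m = 1) | 18.2% | 9.1% | 9.1 points | 2.0 |

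The last row is 20% × 50/55 and 10% × 50/55. It is the upper bound at this loss, because it supposes that every lost patient leaves before any event. The proportional shrinkage does not depend on the assumed risks: with 30% v 10% the difference goes from 20.0 to 18.2 points, again a factor of 50/55.

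**Against sampling error.** With 55 per arm, the standard error of the difference is √[(0.2 × 0.8 + 0.1 × 0.9)/55] = 6.7 points. A shift of at most 0.9 points is about one seventh of that. The odds ratio, which a logistic model would report, moves from 2.25 to 2.22.

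**Uneven loss, all events of lost patients missed.** The split of 2 v 8 patients is an assumption; it keeps the total at the plan's 10.

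- Equal true risk of 20%, loss of 2 v 8: 20% × 53/55 = 19.3% v 20% × 47/55 = 17.1%, a gap of 2.2 points where none exists.
- True 20% v 10%, 8 lost in LCW and 2 in CWO: 17.1% v 9.6%, a difference of 7.5 points.
- True 20% v 10%, 2 lost in LCW and 8 in CWO: 19.3% v 8.5%, a difference of 10.7 points.

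So uneven loss can hide a difference, exaggerate one, or create one.

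**The case against.** The strongest reply is that the carry-forward sentence was written for scheduled measurements. Adverse events are recorded as they arise and have no visit schedule in the article, so a sensible analyst would neither forward a status of no event nor drop a re-operation. The article is also a condensed text, adverse events are neither primary nor secondary endpoints, and many complications of surgery would occur before most patients are lost. All of this limits the size of the problem. It does not remove it, because the article states a rule for all data, names adverse events as an outcome under it, and exempts nothing.

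A reader might infer several stronger things that the article does not support:

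- **That patients never operated on count as event-free.** Randomisation precedes surgery ("After randomization patients will undergo either a CWO HTO or a LCW HTO"), so such patients may exist, and the rule requires their inclusion. But they have no postoperative value to forward, and the article does not say how they are scored.
- **That complications will be charged to the wrong technique.** This would follow under analysis by allocation if someone received the other operation. The article gives no switch rate and does not expect switching; both surgeons are described as experienced in both techniques.
- **That the rule always dilutes the safety comparison.** Even loss shrinks the risk difference but leaves the risk ratio alone. With no loss, no re-operation and no switching, nothing changes.
- **That comparing harms as randomised is wrong.** It is legitimate and keeps the protection of randomisation.

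**Conclusion.** The point holds in a limited form. Carry-forward is the wrong rule for adverse events, and by its wording the article applies it to them. Its use at re-operation sits badly with the article's own definition of an adverse event.

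The effect of loss is probably small. At the plan's 9.1% allowance and assumed risks of 20% v 10%, the difference falls by at most 0.9 points if loss is even, with the risk ratio unchanged. If loss is uneven, the error can go in either direction, by about 2 points or so in the cases shown. These sizes rest on assumed event rates and an assumed pattern of loss. The re-operation part could matter more if applied to the letter, but it is unlikely to be applied so and cannot be sized from the article.

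This is a worthwhile clarification, not a threat to the trial's main conclusions. It is no reason to replace the as-randomised comparison of harms with one by operation received.

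**What to change.** Add a short statement to the Statistics section with these elements:

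- Carry-forward does not apply to adverse events.
- Every event from surgery to one year is counted, including a re-operation itself and anything after it.
- Patients lost before one year are censored at last contact, for example with a Kaplan-Meier one-year risk per arm, if event dates are recorded. Otherwise, the number lost and the time of loss are reported per arm beside the counts.
- The as-randomised comparison stays, and a table among operated patients by technique performed is added.

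The rules for alignment, anatomical and patient-reported outcomes are untouched by this point. The cost is a few lines of text, provided that event dates and the operation performed are recorded; the article does not say that they are, so this should be confirmed. There are two small downsides. The added table is not a strictly randomised comparison if anyone switched, and censoring assumes that loss is unrelated to event risk.

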### Study population

Patients visiting the outpatient clinic of the Orthopedic Department who have an indication to undergo HTO because of osteoarthritis of the medial compartment of the knee with varus alignment will be included if they meet the following criteria: radiologically confirmed medial compartment osteoarthritis, medial joint pain, 6-12° varus alignment and age 18 and older. Exclusion criteria are: symptomatic osteoarthritis of the lateral compartment, rheumatoid arthritis, range of motion of the knee joint under 100°, flexion contracture more than 10°, grade 3 collateral laxity (Insall), history of fracture or previous open operation of the lower extremity, mental incapacity, or inability to fill in the questionnaires in Dutch.

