### Main study parameter/endpoint

Primary outcome measure is the accuracy and preservation correction of the technique, defined by achievement of an overcorrection of 4° valgus one year after surgery as measured by the hip-knee-ankle (HKA) angle. The continuous differences in achievement of a valgus overcorrection and the deviation from 4° valgus will be determined, as well as dichotomous outcome and achievement of a 0-6° valgus alignment .

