## Discussion

Although HTO remains quite successful after 10 years, OA with associated symptoms will progress. Some patients may require total knee replacement (TKR) [15]. Success of TKR for knee OA is well-established, and about 85% of patients are satisfied with the surgical outcome [16], therefore when considering HTO in the early treatment of symptomatic medial compartmental OA subsequent TKA should not be compromised. A randomized clinical trial showed significantly more patellar descent and tibial slope increase after MOW compared to the LCW technique [17]. This may cause exposure and patellar eversion problems during knee replacement that may compromise precision and accuracy of TKR [18]. The advantage of MOW is preservation of bone stock with tensioning of the medial collateral ligament. This may result in a more conservative amount of bone removed during knee joint replacement, so joint line elevation by using a thicker-than-desired tibial component in balancing the ligaments is less likely. Furthermore, unlike LCW, the relative position of the medullary canal is not altered. This may facilitate tibial component placement with intramedullary guidance.

An operative complication that may result in an adverse effect is intraoperative fracturing of the opposite cortex. Avoidance of opposite cortex fracture can be difficult though, and is generally limited by the angular size of the wedge. Opposite cortical fracture occurs often during the LCW technique [15]. A fractured medial cortex in LCW may lead to progressive movement of the distal tibia into a varus position [19]. In case of the MOW, instability at the MOW site due to disruption of the lateral cortical hinge potentially results in displacement of the osteotomy and may contribute to recurrent varus deformity [20]. Newer angular stable plate systems with locking screws seem to avoid this problem. Loss of correction may lead to a suboptimal result [11,21,22]. Still, HTO is considered a very successful surgical procedure with low complication rates. For instance, non-union in HTO is very rare, especially in LCW, and delayed union is seen in about 3-4% [23,24].

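### Carry-forward is applied to re-operated patients, and hardware removal is listed as a re-operation, so observed one-year outcomes would be replaced by earlier values

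*Protocol article*

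**What the plan says.** The carry-forward rule in the Statistics section of the protocol article opens with the words "For those patients who will be lost to follow-up or will be re-operated during follow-up". For this group it prescribes Last Value Carried Forward, and it describes the value to be used only loosely, without saying whether it must precede the re-operation. The rule stands directly after the statement that "All data will be analyzed according to an intention-to-treat principle", which the article explains as including every randomised patient in the group to which that patient was allocated. No exception is made for a re-operated patient who attends at one year.

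Under Other study parameters, "Adverse events like re-operations, including hardware removal, will also be recorded".

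Under Main study parameter/endpoint, "Primary outcome measure is the accuracy and preservation correction of the technique", judged on the HKA angle one year after surgery. Under Study procedures the HKA angle "will be measured after one year on a whole-leg radiograph (WLR) standing on one leg"; no earlier postoperative HKA measurement is listed. Under Study population, inclusion requires "6-12° varus alignment and age 18 and older". Baseline HKA is named in Statistics as a possible confounder, so a preoperative value exists for each patient.

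**The concern.** Re-operation is named as a trigger for carry-forward alongside loss to follow-up. A re-operated patient with no later data is already covered by loss to follow-up, so the separate trigger has an effect only if it overrides data collected after the re-operation. If staple removal counts, patients with a sound correction and a complete one-year visit lose their real outcome.

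For the primary endpoint, the replacement on the article's own schedule is the deformity that the operation was meant to correct. For KOOS, VAS and walking distance, the replacement is a six-week, three-month or six-month value, taken while the patient is still recovering. The endpoint claims to measure preservation of correction, so the one-year film is the observation least suited to being replaced.

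**Working it through.** **1. What is carried forward for HKA.** The article schedules HKA before surgery and at one year. With the one-year value set aside, only the preoperative value remains, 6-12° varus. It lies outside 2-6° valgus for every included patient. It also lies outside 0-6° valgus, the range given under Main study parameter/endpoint, so the discrepancy between the two ranges does not matter here. On the continuous measure, a knee standing at exactly 4° valgus has a deviation of 0°. After overwriting, its deviation is 4 + 6 = 10° to 4 + 12 = 16°.

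**2. The plan's own figure.** Inputs from Sample size calculation: success 60% (closing wedge) and 85% (combined wedge), α = 0.05, power 80%, 50 per arm, 110 in total. Sidedness is not stated; two-sided is assumed. With pooled variance, no continuity correction and mean proportion (0.60 + 0.85)/2 = 0.725:

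n = [1.96·√(2·0.725·0.275) + 0.8416·√(0.60·0.40 + 0.85·0.15)]² / 0.25² = [1.96·0.6315 + 0.8416·0.6062]² / 0.0625 = 48.9, so 49 per arm.

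This agrees with the stated 50. The sample size is not in dispute.

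**3. Effect of overwriting with the preoperative value.** Let q be the share of each arm that is re-operated and overwritten. The documents give no rate, so 5% to 20% is assumed. Re-operated patients are also assumed to have the same true success rate as the rest of their arm. Observed success then becomes p·(1 − q), and

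power = Φ{ [d·√n − 1.96·√(2·p̄(1 − p̄))] / √(p₁(1 − p₁) + p₂(1 − p₂)) },

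where d = p₂ − p₁ and p̄ is the mean of p₁ and p₂. Worked example, q = 0.10 and n = 50: p₁ = 0.54, p₂ = 0.765, d = 0.225, p̄ = 0.6525; numerator 0.271, denominator 0.654, ratio 0.414, power 66%.

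| q in both arms | Closing wedge | Combined wedge | Difference (points) | Power, 50 per arm | Power, 55 per arm |
|---|---|---|---|---|---|
| 0 | 60.0% | 85.0% | 25.0 | 81% | 85% |
| 5% | 57.0% | 80.75% | 23.75 | 73% | 77% |
| 10% | 54.0% | 76.5% | 22.5 | 66% | 70% |
| 20% | 48.0% | 68.0% | 20.0 | 53% | 57% |

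The 55-per-arm column (110/2) is shown because the rule would place all 110 randomised patients in the analysis. It does not model patients truly lost to follow-up, who would also be carried forward from baseline and lower the power again.

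**4. If an early postoperative film existed.** A knee revised for lost correction could then keep its good early angle and count as a success. Suppose half of the re-operated patients are such hidden failures. With re-operation in 10% of the closing-wedge arm and 5% of the combined arm, the rates become 0.60 + 0.05 = 65.0% and 0.85 + 0.025 = 87.5%, a difference of 22.5 points. With 5% and 10%, they become 62.5% and 90.0%, a difference of 27.5 points. All these rates are assumptions, and the premise of an early film is not in the article.

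**The case against.** **The wording is loose.** The rule does not say that the value before re-operation is the one forwarded. For a patient seen at one year, the last available measurement could be the one-year value itself, and then nothing is overwritten. Nor does Other study parameters define re-operation for the analysis; it lists hardware removal among events to be recorded. Both remarks are correct, and they make the reading an inference. It remains the natural one: a separate trigger that never overrides later data would do nothing, and the article offers no narrower meaning of re-operation.

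**Stronger readings that the article does not support.**

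- *The rule hides loss of correction.* The Discussion does say "Loss of correction may lead to a suboptimal result", which makes this tempting. On the stated schedule, however, a revised knee would be given its preoperative varus value and count as a failure. Hidden loss needs an early postoperative film that the article does not list, though the full protocol may provide one.
- *The rule breaches intention to treat.* As the article defines that principle, all randomised patients are analysed in their allocated group, and carry-forward satisfies this. It is open to criticism as imputation, but it does not contradict the definition.
- *The bias falls on one arm.* Fixation uses three staples in the combined technique and two in the closing wedge, so removal rates might differ. Overwriting 10% of the combined arm only would give 0.85 × 0.90 = 76.5% against 60%, a difference of 16.5 points, with power of 42% at 50 per arm and 46% at 55. But both arms carry staples, and nothing in the article supports 10% against none.

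**Conclusion.** The point stands in a limited form and should be corrected. As written, the rule most naturally replaces observed one-year HKA, KOOS, VAS and walking distance with earlier values in any re-operated patient, including one who only had staples removed. For HKA on the stated schedule, that turns an intact correction into a failure.

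The loss of power, to between 73% and 53% at 50 per arm or between 77% and 57% at 55 per arm, rests on three assumptions: a re-operation rate of 5% to 20% that is equal in both arms, success unrelated to re-operation, and the preoperative value being the one carried forward. It illustrates the sensitivity of the result and is not an estimate. The direction of bias would change if an early postoperative film were used, and the article does not settle which value applies.

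**What to change.** Remove re-operation from the carry-forward rule. State that the observed one-year value is analysed for every patient who attends, including after hardware removal.

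For re-operations that themselves change alignment before one year, such as revision osteotomy or knee replacement:

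- count the patient as not achieving 2-6° valgus in the dichotomous analysis;
- prespecify one handling for the continuous HKA angle and the deviation from 4°, with a sensitivity analysis, since a failure classification supplies no value for these measures;
- report these re-operations by arm.

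The change is to wording and needs no new visits or measurements. Re-operations are already recorded; the small added burden is to record the reason for each one so that it can be classified.

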#### Lateral closing wedge osteotomy (LCW)

For the lateral closing wedge HTO, instrumentation of Allopro (Zimmer; Winterthur, Switzerland) will be used. The common peroneal nerve will be exposed and snared with a nerve band. Next, the anterior part of the proximal fibular head (anterior part of the proximal tibiofibular syndesmosis) will be resected. The osteotomy will be made and the wedge taken out. The osteotomy will be fixated with two staples. At the end of the procedure a fasciotomy of the anterior compartment will be performed to prevent compartment syndrome.

The postoperative treatment for both HTO techniques consists of a pressure bandage for 24 hours and cast immobilization until removal of the stitches, followed by flexion-extension brace protection and 50% weight bearing for 6 weeks. After this period, weight bearing can be built up to 100% based on the pain sensation of the patient, brace use can be reduced to no brace, and physical therapy will be started.

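### Last value carried forward is applied to an HKA outcome scheduled only at baseline and one year, so unless earlier postoperative films exist each lost patient is scored with the preoperative varus angle

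*Protocol article*

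**What the plan says.** The Statistics section analyses all randomised patients in their allocated arm. For patients lost or re-operated during follow-up, "the last available measurement or the last measurement will be forwarded (Last Value Carried Forward technique"). The rule is general and no outcome is exempt.

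Under Study procedures, the primary outcome, the HKA angle, is "measured after one year on a whole-leg radiograph (WLR) standing on one leg". The only other HKA value named is the baseline value, listed in Statistics as a possible confounder. Visits also take place at six weeks and six months, but the article describes them with routine physical examination only. Tibial slope, patellar height and leg length are listed at one year after surgery. VAS, KOOS and walking distance are listed at six weeks, three months, six months and one year.

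Entry requires 6-12° of varus (Study population). On success, the Sample size calculation says: "A successful operative result is defined as achievement of a 2-6° valgus alignment". The same section plans for an "expected increase of the success rate from 60% in the closed wedge HTO to 85% in the combined wedge HTO" and concludes "we need to include 50 patients in each study group". It then adds: "To adjust for possible loss to follow-up, a total of 110 patients will be included in the study".

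**The concern.** Carrying a value forward is meaningful only if the carried value measures the same state as the missing one. Surgery lies between the two HKA readings that the article names. Carrying the first into the place of the second records that the osteotomy corrected nothing. Because the entry range (varus) and the success range (valgus) do not overlap, the result for every such patient is fixed in advance. This also holds under the 0-6° valgus range given in the Main study parameter section.

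Three things are at stake:
- The contrast between arms is diluted when losses are equal and biased when they are not.
- Ten patients were added to protect power, but the Statistics rule keeps lost patients in the denominator as failures.
- In the linear model of postoperative alignment, carried values are extreme outliers and are treated as if observed, so standard errors are wrong as well.

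The rule also covers re-operated patients, and Other study parameters counts hardware removal as a re-operation. The text does not say what happens to a one-year film obtained after such a procedure.

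**Working it through.** **Inputs from the protocol article.** Success 60% (LCW) and 85% (CWO), α 0.05, power 80%, 50 per arm, 110 in total (55 per arm), entry 6-12° varus, target 4° valgus.

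**Assumptions.** A two-sided test. A loss of 5 of 55 per arm, because the allowance implies 10/110 = 9.1% and no rate is stated. For the linear model, a completer mean of 4° valgus and SD of 2°, and an SD of 1.7° among the carried baseline angles.

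**1. The plan's own figure.** With pooled variance and no continuity correction, n = [1.96·√(2·0.725·0.275) + 0.842·√(0.60·0.40 + 0.85·0.15)]² / 0.25² = 48.9, so 49 per arm. The stated 50 is reproduced. Power is 80.9% at 50 per arm and 84.5% at 55 per arm with no loss.

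**2. Equal losses, baseline carried forward.** Each arm's rate becomes p·(1 − d), with all 55 analysed. At d = 5/55:
- LCW: 0.60·50/55 = 54.5%. CWO: 0.85·50/55 = 77.3%. Difference: 22.7 points.
- SE under the null = √(2·0.659·0.341/55) = 0.0904. SE under the alternative = √((0.545·0.455 + 0.773·0.227)/55) = 0.0878.
- Power = Φ[(0.2273 − 1.96·0.0904)/0.0878] = Φ(0.57) = 71.6%.

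| Losses per arm (of 55) | Rates | Power, baseline carried |
|---|---|---|
| 0 | 60.0% v 85.0% | 84.5% |
| 1 | 58.9% v 83.5% | 82.0% |
| 2 | 57.8% v 81.9% | 79.5% |
| 5 | 54.5% v 77.3% | 71.6% |

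Analysing only the 50 observed per arm keeps the 25 points and 80.9% power. Holding 80% under the carry-forward rule at 9.1% loss would take 68 per arm (136 in total).

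**3. Unequal losses, 10 in total.**
- 3 LCW, 7 CWO: 0.60·52/55 = 56.7% and 0.85·48/55 = 74.2%. Difference 17.5 points, power 48.6%.
- 7 LCW, 3 CWO: 52.4% and 80.4%. Difference 28.0 points, power 88.5%.
- No true difference, both 85%, losses 3 and 7: 80.4% and 74.2%, a spurious 6.2 points. The two-sided test rejects 12.0% of the time instead of 5%. With both at 60%: 4.4 points and 7.4%.

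**4. Linear model.** A carried baseline lies 4 + 6 = 10° to 4 + 12 = 16° from target. Five of 55 shift an arm's mean towards varus by 0.0909·10 = 0.9° to 0.0909·16 = 1.5°. The variance is (1 − d)·2² + d·1.7² + d·(1 − d)·D², where D is that distance:
- D = 10: √(3.64 + 0.26 + 8.26) = 3.5°.
- D = 16: √(3.64 + 0.26 + 21.16) = 5.0°.

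The SD therefore rises from 2° to about 3.5-5.0°.

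**5. Secondary outcomes.** Slope, patellar height and leg length follow the HKA pattern, since no postoperative value before one year is listed. For VAS, KOOS and walking distance, the carried value is the last one collected at six weeks, three months or six months. For a patient lost soon after six weeks, that value falls in early recovery, since aftercare includes "flexion-extension brace protection and 50% weight bearing for 6 weeks".

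**The case against.** The strongest counter-argument is that the article states when the primary outcome is read, not that no other film is taken. It speaks of preservation of the correction, which is hard to judge without an early postoperative angle, and it condenses a fuller protocol in which an imaging schedule would normally sit. This stands as a condition on the finding. A reader might infer that no earlier postoperative HKA exists; the article schedules none but does not exclude it. If early films exist, the certain failure and the figures above no longer apply. The rule would then carry an early angle to one year and hide later loss of correction, which the Discussion itself names as a risk. It would remain unsuitable for an endpoint about preservation.

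Other stronger readings also fail:
- That the ten extra patients give no protection. At 9.1% loss under the rule, power is 71.6% with 55 per arm and 67.4% with 50. They help, but not enough to keep 80%.
- That the bias always works against CWO. It goes either way, and with equal losses it is a conservative dilution.
- That six-week scores are always carried forward. This applies only to patients with no later value.
- That an SD of about 4° is a finding. It depends on assumed inputs, hence the range.

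It is also fair to say that counting re-operation as a failure can be a deliberate choice. If so, it should be stated as such. Carry-forward does not express it clearly, and deleting the rule without a replacement would leave re-operation unaddressed.

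**Conclusion.** The concern holds, conditional on the schedule as the article gives it. With HKA named only at baseline and one year, the stated rule scores a patient lost before one year as a certain failure, 10-16° off target. This is the effect of a rule that is written down, not of a detail left to another document.

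At the loss implied by the allowance, the planned 25 points shrink to 22.7 and power to about 72%, so the article's two statements on loss do not fit together. Power is already just under 80% at two losses per arm. Unequal losses can understate or overstate the effect and can raise the type I error above 5%.

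The rates, α and group sizes are the article's own. The loss rate, its split between arms, two-sidedness, and the HKA mean and SDs are assumptions. The sample size calculation itself is not wrong.

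**What to change.** Remove last value carried forward and replace it as follows.

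1. **HKA.** Analyse the observed one-year HKA in the allocated arm for every patient who has one, including re-operated patients. Multiply impute missing values from arm, baseline HKA, age and sex, plus any early postoperative HKA if the full protocol collects it.
2. **Sensitivity analyses for the dichotomous outcome.** Missing counted as failure and, separately, re-operation counted as failure.
3. **VAS, KOOS and walking distance.** One linear mixed model over all collected time points with baseline as covariate, reading off the one-year contrast.
4. **Slope, patellar height and leg length.** Observed one-year values with the same imputation approach as HKA.

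The cost is a change of wording and slightly more analysis work. The main methods rest on a missing-at-random assumption, and if HKA exists only at baseline and one year, imputation will recover little beyond the observed cases. The missing-as-failure analysis shows how far the dichotomous conclusion depends on that assumption. On that outcome it gives the same result as carrying baseline forward for lost patients, so the pessimistic view is kept but no longer drives the primary comparison.
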